### Exploratory analyses

We hope the BaSICS trial will provide relevant information on fluid management in critically ill patients. However, additional analyses that explore potential mechanisms and confounders are planned to aid in study interpretation. These analyses are expected to be reported separately.

- Mean adjusted chloride load (MACL): MACL, defined as total infused chloride over the total volume of infused fluids, is expected to be related to the randomization arm since Plasma-Lyte 148 has 98mEq/L and normal saline has 154mEq/L. It has been suggested that MACL can mediate the effect of saline on outcomes;^(13)^ that is, by using saline, the MACL will be higher (and will approach 154mEq/L if only saline is used), and a higher MACL can cause harm. Based on the daily infusion of fluids used per patient, including all open-label infusions, we will estimate the daily MACL and the cumulative MACL effects on mortality in a time to event analysis for the ICU and for in hospital mortality. We intend to adjust a Cox proportional hazard frailty model and test the incremental effect of the daily and accumulated MACL and total fluid infusion volume as a time-dependent variable until day 3. This analysis will, therefore, consider both the total volume of infused fluids and the MACL and will explore both potential factors on short-term outcomes. Splines will be considered when modeling.- Chloride subgroup analysis: It is also conceivable that serum chloride may be a driver of organ failure and that part (or all) of the effects of the fluid type intervention is mediated by serum chloride; that is, harms of saline may be more prominent in patients with higher baseline serum chloride. We plan to tackle this issue initially with a sensitivity analysis among patients with low and high (> 110mEq/L) baseline serum chloride for the primary endpoint and the renal secondary endpoints. It should be highlighted that the measurement of serum chloride was not obligatory in BaSICS and therefore not all patients will be available for this analysis.- Bayesian network for SOFA (total, and all components except hepatic): Death is a competing event for SOFA measurements over time. One approach^(14)^ is to draw Bayesian networks for each intervention arm and to observe transitions to possible states at D2, D3 and D7 according to the randomization group (for both arms) while accounting for death as an absorbent state. This approach can answer, for example, what is the probability that a patient who has a baseline hemodynamic SOFA of 3 and received a slow infusion is alive without vasopressors (alive and SOFA < 3) at day 3? We can obtain relative risks and 95% confidence intervals through bootstrapping the data set. Total SOFA will be categorized for this analysis in quartiles. SOFA components are planned to be used as 5 level categorical variables.

Hemodynamic substudy: A subgroup of ICUs collected blood pressure, central venous pressure, heart rate and several other parameters to address tissue perfusion immediately after every bolus infusion and each half hour until one hour after total infusion of the 500mL bolus. This primary study endpoint was defined as the mean blood pressure within one hour after fluid expansion, focusing on infusion speeds (slow *versus* fast). We intend to use generalized mixed linear models for all continuous variables to address individual repeated measures over time for the intercept and/or slope by infusion, nested with patients without covariates. Mean blood pressure shall be well fitted as a normal distribution.

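### The split on baseline serum chloride is offered as a look at mediation, but it can only show effect modification; it should be relabelled and tested with an interaction term

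*SAP article*

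**What the plan says.** The item is the chloride subgroup analysis in the Exploratory analyses section of the SAP article. It makes four statements in sequence.

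- **Hypothesis:** serum chloride may drive organ failure, and "part (or all) of the effects of the fluid type intervention is mediated by serum chloride".
- **Restatement, introduced as if equivalent:** "harms of saline may be more prominent in patients with higher baseline serum chloride".
- **Analysis:** "We plan to tackle this issue initially with a sensitivity analysis among patients with low and high (> 110mEq/L) baseline serum chloride", carried out "for the primary endpoint and the renal secondary endpoints".
- **Caveat:** "the measurement of serum chloride was not obligatory in BaSICS and therefore not all patients will be available for this analysis".

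The section introduces all its items by saying that "additional analyses that explore potential mechanisms and confounders are planned to aid in study interpretation", and expects them to be reported separately. The Introduction says important mediators are expected and that the SAP is an opportunity to define beforehand how they will be handled.

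The preceding item concerns mean adjusted chloride load (MACL), which is chloride infused per volume infused. It plans to "test the incremental effect of the daily and accumulated MACL and total fluid infusion volume as a time-dependent variable until day 3". That exposure arises after randomisation, but it is not serum chloride.

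**The concern.** Mediation is a statement about what happens after allocation: the fluid changes serum chloride, and the changed chloride changes outcome. Variation of the fluid effect across baseline chloride is effect modification. Either can be present without the other, yet the plan treats the second as a restatement of the first.

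If the mediation wording stays, a flat result across the two groups could be taken as evidence against a chloride mechanism, and a difference as support for one. Neither inference follows from the split alone.

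The item also states no test that compares the two groups. It is headed a subgroup analysis but described in the text as a sensitivity analysis. The Subgroup analyses section promises interaction p-values for six listed subgroups and for the primary outcome only. Baseline chloride is not among the six, and the renal endpoints are not covered. Two separate results with no comparison leave room for a conclusion based on significance in one group only.

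**Working it through.** **1. The plan's own figure.** The chloride item gives no number to reproduce. The article's one reproducible design figure is 89% power for a hazard ratio of 0.9 with 11,000 patients and 35% control mortality (Sample size calculation section).

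- Risk on the experimental side: 1 − 0.65^0.9 = 0.321.
- Events: 5,500 × (0.350 + 0.321) ≈ 3,693.
- Power at two-sided 5% (assumed two-sided): Φ(√3,693 / 2 × |ln 0.9| − 1.96) = Φ(3.20 − 1.96) ≈ 89.3%.

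The figure reproduces. The present point does not depend on it, except that 89% serves as one end of the range in step 4.

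**2. What the split can see if chloride carries the whole effect.** Let C0 be baseline chloride, let saline raise it by δ, and let the log odds of death depend on later chloride through a function g. The saline effect at a given baseline is then g(C0 + δ) − g(C0).

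- If g is linear with slope β, this equals βδ. C0 drops out, and the expected difference between low and high groups is zero despite full mediation.
- If g is convex or has a threshold, the effect grows with C0, and full mediation does show up as a difference by baseline.

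The result of the split therefore depends on the shape of g, which the plan does not state.

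**3. Illustrative simulation.** There were 2,000,000 patients per scenario, and every parameter is an assumption. Baseline chloride is normal with mean 104 and SD 6 mEq/L. Saline adds 4 mEq/L, with noise of SD 2. The intercept of the log odds is −0.65, a risk of about 34%. The low group is taken as 110 mEq/L or below. Entries are log odds ratios for saline against balanced solution.

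| Scenario | Low | High | Difference |
|---|---|---|---|
| (a) Fully mediated, linear, slope 0.0263 per mEq/L (0.0263 × 4 = 0.105) | 0.107 | 0.107 | 0.000 |
| (b) No mediation; direct effect 0.1, plus 0.2 above 110 | 0.101 | 0.296 | 0.195 |
| (c) No mediation; uniform direct effect 0.105 | 0.103 | 0.110 | 0.006 (before rounding) |

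The small difference in (c) is simulation noise. About 15.9% of patients lie above 110 (one SD above the mean), roughly 317,000. With a risk near 0.35, the standard error of the difference is about √[4/(317,000 × 0.2275) + 4/(1,683,000 × 0.2275)] ≈ 0.008.

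Scenarios (a) and (c) cannot be told apart, although one is all mediation and the other none. Scenario (b) shows a clear difference with no mediation.

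**4. Reading two groups separately.** Suppose the true effect is the same in both groups and each separate test has power p. The chance that exactly one is significant is 2p(1 − p).

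| Power per group | Calculation | Exactly one significant |
|---|---|---|
| 20% | 2 × 0.20 × 0.80 | 32% |
| 50% | 2 × 0.50 × 0.50 | 50% |
| 80% | 2 × 0.80 × 0.20 | 32% |
| 89% | 2 × 0.89 × 0.11 | about 20% |

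The article gives no power for these groups, so the range is illustrative. Equal power in both groups is a further simplification, and 50% is the maximum of the formula under it.

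**The case against.** The strongest reply is that the restatement supplies the working question, whether saline does more harm at higher baseline chloride, and a baseline split addresses exactly that. This stands: the analysis is mislabelled, not useless. A reader might infer that it cannot answer anything the plan asks, and the text does not support that.

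Second, the baseline prediction can follow from the mechanism. If harm rises more steeply at high chloride, the same rise does more damage in patients who start high. This also stands as a possibility, and it means the zero difference in scenario (a) is one case and not a general result. It does not make the split specific for mediation, because scenario (b) produces a difference without any.

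Third, the item is called an initial step, is exploratory and is reported separately, and the MACL item examines a post-randomisation chloride exposure. All true. MACL measures chloride infused, however, so it does not supply the missing link to serum chloride.

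Fourth, the absent interaction test is inferred from silence in a condensed article, and the subgroup heading could be read as importing the trial's general convention. That is partly fair. The convention as written covers neither this variable nor the renal endpoints, so the gap remains. Nothing says that separate p-values will be compared, and the risk in step 4 is a possibility only.

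Finally, a prespecified cut-point in an exploratory subgroup is conventional and matches other splits in the plan. Modelling chloride as continuous is a preference, not the correction of an error.

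**Conclusion.** The point holds as one of labelling and inference. A baseline value can modify the fluid effect but cannot mediate it, so the planned split does not by itself bear on mediation in either direction. It can bear on whether saline is more harmful at higher baseline chloride.

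The logical part needs no numerical assumption. The simulated log odds ratios rest wholly on assumed parameters and only show that each pattern can occur. The 20% to 50% range for significance in one group only assumes equal true effects and equal power per group.

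A reader might go further and infer that the trial will draw a false conclusion about mechanism, or that its main results are exposed. The documents do not support this. The article does not say how a null or positive split will be interpreted, it admits that chloride data are incomplete, and no primary or secondary conclusion rests on the item. This is a minor correction, worth making because the Introduction presents advance definition of mediator analyses as something this SAP is meant to provide.

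**What to change.** - Describe the item throughout as a subgroup analysis of effect modification by baseline serum chloride. Remove the statement that it examines mediation, and say that it does not address it.
- Among patients with baseline chloride measured, test one fluid-by-baseline-chloride interaction in the primary mixed Cox model and one in each renal model: the mixed Poisson model for renal replacement therapy, and the mixed logistic models for acute kidney injury at days 3 and 7.
- Preferably enter chloride as continuous, and keep the 110 mEq/L split to display estimates with confidence intervals.
- State that interaction p-values are reported for this item, since the Subgroup analyses section covers neither baseline chloride nor the renal endpoints.

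The cost is a few sentences in the SAP and one model term per endpoint, on baseline data already held for the patients concerned. A formal mediation analysis on post-randomisation serum chloride is not requested, because the article does not show that such measurements were collected.

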### Study background and flowchart

BaSICS is a large pragmatic critical trial that aims to provide evidence for or against the use of Plasma-Lyte 148 over 0.9% saline and of lower infusion speeds during fluid challenges in critically ill patients. Patients were randomized using a web-based system designed for the trial in a factorial way (blocks of 12 patients), stratified by recruiting site in a 1:1:1:1 ratio to both define a specific fluid group (Plasma-Lyte 148 or 0.9% saline) and slow (333mL/h) or rapid (999mL/h) infusion during a fluid challenge.^(1)^ The details of the inclusion and exclusion criteria have been addressed in the original protocol, together with recommendations for fluid management and safety rules.^(1)^ The planned flowcharts for both interventions are shown in figures 1 and 2, respectively. BaSICS is a large pragmatic trial, and a screening log was not obtained at each site due to the large number of included patients and for local logistics reasons.

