### Primary outcome analysis

Mortality until 90 days will be tested using mixed-effects Cox proportional hazard models, considering sites as the random variable (frailty models)^(3)^ adjusted for age, baseline SOFA^(4)^ score and the type of admission (planned admission, unplanned admission with baseline sepsis and unplanned admission without baseline sepsis). Sepsis will be defined as infection plus organ failure as per the Sepsis 3 criteria.^(2)^ Proportionality of the hazard ratio will be assessed using the Grambsch and Thernau method,^(5)^ and interactions between the intervention arms (infusion solution and speed) will be tested on this model. If the interaction parameter is significant, we intend to report only one manuscript describing “inside the table” effects, that is, exploring all the four possible combinations and their effects on mortality. If the interaction parameter is not significant at the 5% significance level, marginal effects for each group will be highlighted. In this case, “inside the table” effects shall be reported as supplementary material following CONSORT recommendations for 2 × 2 factorial designs.^(6,7)^ Kaplan-Meier curves will be presented comparing the four arms and separated considering only Plasma-Lyte® *versus* Saline, and Slow *versus* Rapid infusion. Patients with missing follow-up at 90-days will be added to the main primary outcome analysis and censored at their last known follow-up time, patients without discharge information will be imputed by chained equations method using site, age, baseline SOFA score and type of admission.

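### The haemodynamic substudy model excludes covariates and names no site term, although randomisation was stratified by site and baseline covariates are in hand; precision may be lost for no stated reason.

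*SAP article*

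**What the plan says.** Under Exploratory analyses, the hemodynamic substudy paragraph says "A subgroup of ICUs collected blood pressure, central venous pressure, heart rate" and other perfusion measures. Readings were taken "immediately after every bolus infusion and each half hour until one hour after total infusion of the 500mL bolus". The endpoint is "mean blood pressure within one hour after fluid expansion, focusing on infusion speeds". The model is a generalised linear mixed model with repeated measures "nested with patients without covariates". On the distribution the text says "Mean blood pressure shall be well fitted as a normal distribution", so for this endpoint it is in effect a normal linear mixed model. Site is not mentioned, and no reason is given for leaving covariates out.

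Elsewhere in the same article:

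- Study background and flowchart: patients were randomised "stratified by recruiting site in a 1:1:1:1 ratio", in blocks of 12.
- Primary outcome analysis: site is a random effect (frailty), with adjustment for age, SOFA at baseline and admission type.
- Secondary outcomes and Tertiary outcomes: the models for acute kidney injury, for ICU and hospital mortality and for length of stay each name site as a random effect.
- The opening of Exploratory analyses says these analyses are to be published apart from the main results.

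**The concern.** The substudy departs from the plan's usual practice without explanation. It too is multi-site and uses the site-stratified allocation, but its model is the one that rules covariates out in words.

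Infusion speed is allocated to the patient, so slow versus rapid is a comparison between patients. Further boluses and half-hourly readings average out noise within a patient. They leave untouched the differences between patients, which baseline covariates and site can reduce.

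The article gives some ground for expecting those differences to matter. Low blood pressure or vasopressor use is only one of several alternative risk factors for entry, so patients with and without shock enter the same comparison. The Bayesian network item in the same section reads a haemodynamic SOFA below 3 as being off vasopressors, so baseline SOFA carries some information on circulatory state.

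At stake is the width of the interval for the substudy's own endpoint, and whether adjustment is fixed in advance. Covariates added after the data are seen would be post hoc, which is what this SAP sets out to prevent.

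**Working it through.** **The plan's own figure.** The substudy has no stated size or power, so there is nothing on this point to reproduce. The only power figure is the main trial's 89%. With 5,500 patients per side, 35% control mortality and a hazard ratio of 0.9, the treated risk is 1 − 0.65^0.9 = 0.3214. Events are 5,500 × (0.35 + 0.3214) = 3,693. Schoenfeld power at two-sided 5% is Φ(½ × √3,693 × |ln 0.9| − 1.96) = Φ(1.24), or 89.3%. It reproduces, but has no bearing on the substudy.

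**Why repeated readings do not help here.** With n patients per arm and k readings each, the variance of the arm difference is about (2/n)(σ_b² + σ_w²/k), where σ_b² is the variance between patients and σ_w² that within patients. As k grows, 2σ_b²/n remains. Site and baseline covariates act on σ_b².

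**Size of the loss.** Let R² be the share of the variance of the patient-level mean pressure that site and baseline covariates explain together. Adjustment multiplies the standard error by √(1 − R²), so the unadjusted interval is wider by 1/√(1 − R²) − 1. The documents give no R²; the values below are assumptions. The last column starts from a comparison with 80% power unadjusted and computes Φ((1.96 + 0.84)/√(1 − R²) − 1.96).

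| Assumed R² | Unadjusted interval wider by | 80% power becomes |
|---|---|---|
| 0.02 | 1.0% | 80.8% |
| 0.05 | 2.6% | 82.0% |
| 0.10 | 5.4% | 84.0% |
| 0.20 | 11.8% | 87.9% |
| 0.30 | 19.5% | 91.8% |
| 0.40 | 29.1% | 95.1% |

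**Check by simulation.** Assumed: 10 sites of 24 patients, 1:1 allocation balanced within site, patient-level SD 12, no true effect, 4,000 runs, one mean per patient. The adjusted analysis used fixed site terms and one covariate.

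| Site ICC | Covariate R² | Mean SE, unadjusted / adjusted | Type I error, unadjusted / adjusted |
|---|---|---|---|
| 0.02 | 0.02 | 1.55 / 1.52 | 4.5% / 4.6% |
| 0.05 | 0.05 | 1.54 / 1.47 | 5.0% / 5.4% |
| 0.10 | 0.10 | 1.54 / 1.39 | 4.2% / 5.0% |
| 0.10 | 0.20 | 1.54 / 1.30 | 3.5% / 4.9% |

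The Monte Carlo error on a 5% rate is √(0.05 × 0.95/4,000), about 0.3 percentage points. The mean unadjusted estimate stayed within 0.02 of zero throughout, so there is no bias. In the last row 1.543/1.298 = 1.19, which agrees with the 19.5% in the first table at R² = 0.10 + 0.20 = 0.30.

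The conservatism comes from site. Stratified allocation removes site differences from the true variability of the contrast, but a model without site leaves them in the standard error. In the last row the empirical SD of the unadjusted estimate was 1.459 against a mean SE of 1.543.

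**The case against.** The strongest reply is that nothing here is invalid. An unadjusted comparison in a randomised substudy is unbiased, a model fixed without covariates leaves no analyst discretion, and the paragraph is a short one in a condensed article about an exploratory analysis. All of that stands, and it limits the point to a minor one. It does not supply a reason for excluding covariates that are already collected.

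A reader might infer four stronger claims that the documents do not support.

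- **That site is excluded.** The text rules out covariates and is silent on site. Elsewhere the plan names site as a random effect separately from the adjustment covariates, so the phrase does not by itself exclude it. Site is unmentioned, no more.
- **That chance imbalance in severity biases the speed effect.** Chance imbalance is random error, and the unadjusted standard error already allows for it.
- **That a definite gain can be claimed.** A correlation of 0.3 to 0.5 between baseline and pressure would cut variance by 9% to 25%, but no such correlation is given. Baseline covariates do not reduce within-patient variation, and later boluses are further from the baseline values.
- **That pre-bolus pressure, or hypotension or vasopressor status at entry, is available for adjustment.** The substudy paragraph names only readings after the bolus. The entry criterion is one of several alternatives and has no row in Table 1, so complete recording is not shown.

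**Conclusion.** The point holds as a minor one. The substudy model excludes covariates in words, names only patient nesting, and gives up whatever precision site and the primary model's covariates would bring, without saying why. The slow-versus-rapid estimate remains unbiased; the cost is a wider interval and, if ICUs differ in mean pressure, a slightly conservative test.

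The size is unknown. The range of about 1% to 29% in interval width rests wholly on an assumed R² of 0.02 to 0.40, and at the lower end the loss is negligible. The calculation also assumes a normal linear model and a patient-level contrast; both follow from the text. Because the analysis is exploratory, no primary or secondary conclusion of the trial is affected.

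**What to change.** In the hemodynamic substudy paragraph, delete the words that exclude covariates. State that the model has a random intercept for site, with patients nested in sites, and adjusts for age, baseline SOFA and admission type as in the primary outcome model. Add a pre-bolus pressure only if the substudy recorded one. If the authors prefer the unadjusted model, they should give the reason and say whether site enters.

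The cost is a sentence in the SAP and one line of model code, settled before the substudy data are analysed. No new data are needed.

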## CONCLUSION

This manuscript outlines the statistical analytical plan for the BaSICS randomized controlled trial, including all primary, secondary and tertiary objectives. Details of subgroup analyses and potential exploratory analyses are also provided.

